## Abstract

**Background:**

Fatigue is one of the most commonly reported and debilitating symptoms of multiple sclerosis (MS); approximately two-thirds of people with MS consider it to be one of their three most troubling symptoms. It may limit or prevent participation in everyday activities, work, leisure, and social pursuits, reduce psychological well-being and is one of the key precipitants of early retirement. Energy effectiveness approaches have been shown to be effective in reducing MS-fatigue, increasing self-efficacy and improving quality of life. Cognitive behavioural approaches have been found to be effective for managing fatigue in other conditions, such as chronic fatigue syndrome, and more recently, in MS. The aim of this pragmatic trial is to evaluate the clinical and cost-effectiveness of a recently developed group-based fatigue management intervention (that blends cognitive behavioural and energy effectiveness approaches) compared with current local practice.

**Methods/Design:**

This is a multi-centre parallel arm block-randomised controlled trial (RCT) of a six session group-based fatigue management intervention, delivered by health professionals, compared with current local practice. 180 consenting adults with a confirmed diagnosis of MS and significant fatigue levels, recruited via secondary/primary care or newsletters/websites, will be randomised to receive the fatigue management intervention or current local practice. An economic evaluation will be undertaken alongside the trial. Primary outcomes are fatigue severity, self-efficacy and disease-specific quality of life. Secondary outcomes include fatigue impact, general quality of life, mood, activity patterns, and cost-effectiveness. Outcomes in those receiving the fatigue management intervention will be measured 1 week prior to, and 1, 4, and 12 months after the intervention (and at equivalent times in those receiving current local practice). A qualitative component will examine what aspects of the fatigue management intervention participants found helpful/unhelpful and barriers to change.

**Discussion:**

This trial is the fourth stage of a research programme that has followed the Medical Research Council guidance for developing and evaluating complex interventions. What makes the intervention unique is that it blends cognitive behavioural and energy effectiveness approaches. A potential strength of the intervention is that it could be integrated into existing service delivery models as it has been designed to be delivered by staff already working with people with MS. Service users will be involved throughout this research.

**Trial registration:**

Current Controlled Trials ISRCTN76517470

## Background

Multiple sclerosis (MS) is a chronic, unpredictable, incurable, demyelinating disease of the central nervous system affecting approximately 2.5 million people [1-3]. It is more common in women and onset peaks between 20 and 40 years. The causes and early development of the disease are not fully understood but probably involve immune, genetic, and environmental factors [2,3]. Fatigue is one of the most commonly reported and disabling symptoms of MS, often occurring daily [4] and with a variable course [5,6]. Up to 86% of individuals with MS experience fatigue at any one time; 65% consider it to be one of their three most troubling symptoms [4].

Fatigue has been defined as a 'subjective lack of physical and/or mental energy that is perceived by the individual or caregiver to interfere with usual or desired activities', p. 2 [7]. The pathophysiology of fatigue is unclear [8] but likely to be multi-factorial [9,10]. Findings on the relationships between fatigue and other clinical variables (such as age, gender, disease duration, and clinical activity) have been equivocal [11].

Researchers have distinguished between primary and secondary fatigue [12]. 'Primary' fatigue relates to aspects of fatigue deemed to be directly related to the disease process such as lassitude or asthenia (an overwhelming sense of tiredness not directly related to participation in activity or exercise), 'short-circuiting' fatigue (when muscular performance deteriorates during sustained activity but recovers after a short rest break) and heat sensitive fatigue (where fatigue is triggered or worsened by heat).

'Secondary' fatigue refers to fatigue that is not unique to MS and is related to factors common to a range of chronic and disabling conditions (e.g. sleep disturbance, medication side effects, infection, physical exertion, depression, anxiety, stressful life events, characteristics of the local environment - such as lighting and temperature within a work setting). The relationship between these dimensions is complex; various symptoms of MS may act as predisposing factors for secondary fatigue.

Fatigue may limit or prevent participation in everyday activities, work, leisure and social pursuits, restrict role fulfilment and reduce psychological well-being [12,13] and is one of the key precipitants of early retirement [14,15]. Its 'invisible' nature may lead to difficulties in personal and work relationships [16,17].

Fatigue is highly related to an individual's sense of control over MS and psychological well-being [13,18,19]. Sense of control has been found to predict lower levels of fatigue [20], suggesting that increasing self-efficacy related to fatigue could improve quality of life.

Pharmacological and non-pharmacological treatments are available for MS-related fatigue, but evidence on effectiveness is mostly inconclusive or non-existent [4,21,22]. Non-pharmacological studies exploring the effectiveness of energy conservation programmes for MS-fatigue have tended to be small and uncontrolled [23-27]. Two fatigue management initiatives have been developed in the UK [28,29]. Only the former has been evaluated and numbers were small. In the USA, a randomised controlled trial (RCT) [30] of an energy conservation course [31] found evidence for its effectiveness in reducing fatigue impact, increasing self-efficacy and aspects of quality of life; benefits were maintained at 1 year [32]. Results from a German adaptation were also promising [33]. A RCT that evaluated a multi-disciplinary fatigue management programme [34] demonstrated no reduction in fatigue impact compared with a placebo intervention.

Although the important relationships between physical and psychological aspects of MS-fatigue are recognised [35], high quality RCTs of psychological interventions are rare [36]. In Chronic Fatigue Syndrome (CFS) individual Cognitive Behavioural Therapy (CBT) is effective in treating fatigue [37,38]. A systematic review [39] of psychological interventions for MS identified just one RCT that used a cognitive behavioural approach to manage MS-fatigue [40]. The intervention consisted of individual CBT conducted by a clinical psychologist and was shown to be effective in reducing fatigue. However, in the UK National Health Service (NHS), and elsewhere, psychologists working with people with MS are scarce, thus this approach may prove impractical [39].

A number of pilot studies have used group-based cognitive behavioural approaches, either in the context of coping with MS [41-43], or specifically with MS-fatigue [44]. Group-based approaches are potentially more cost effective than one-to-one and offer opportunities for peer support. Recently, we have developed a group-based manualised fatigue intervention for the management of MS-fatigue that incorporates energy effectiveness and cognitive behavioural approaches [45]. This intervention involves health professionals routinely involved in the management of MS, supported by clinical psychologists, and is thus compatible with a wide range of existing health service structures (such as the UK National Health Service (NHS)). Pilot work has been encouraging and this trial is a formal evaluation of the effectiveness of the intervention [45].

### Aims

Patient population: Adults with multiple sclerosis experiencing significant fatigue that is impacting on daily life.

#### Primary aim

1. To test whether those allocated to the group-based cognitive behavioural fatigue management intervention differ (in terms of fatigue severity, self-efficacy, and MS-specific quality of life) from those allocated to current local practice.

#### Secondary aims

2. To test whether those allocated to a group-based cognitive behavioural fatigue management intervention differ (in terms of fatigue impact, mood, general quality of life, and activity patterns) from those allocated to current local practice.

3. To assess how the group-based cognitive behavioural intervention and current local practice differ in terms of cost-effectiveness.

4. For those who attend the group-based programme, to gather feedback about experiences of attending the programme, any changes made and barriers to change encountered, and helpful or unhelpful aspects.

## Methods/Design

### Trial design

This is a parallel arm randomised controlled trial comparing a group-based cognitive behavioural approach to managing fatigue (Fatigue Management Programme (FMP)) with current local practice. The trial design is summarised in Figure 1.

**Figure 1 F1:**
[figure not shown]
**Flowchart of trial design**.

This RCT is the fourth stage of a research programme that has followed the Medical Research Council (MRC) guidance for developing and evaluating complex interventions [46]. The pilot work has been published [45].

Participants will be randomised to receive the fatigue management intervention or current local practice. A placebo arm to the trial was considered but rejected because (a) the fatigue management programme is a "complex intervention" (incorporating group, educational, cognitive, behavioural, and energy effectiveness components and the attendance of supportive others) making it difficult to know which "active ingredients" to control for in the placebo; (b) of the difficulties inherent in designing a placebo intervention that is credible to participants and facilitators, and that maintains participant masking, and (c) in clinical practice, the costs of delivering the fatigue management programme and the sham intervention would be equivalent.

The pilot research (multi-centre pilot) undertaken identified practical difficulties involved in running a three centre randomised trial. The multi-centre approach for the randomised trial will help to ensure sufficient numbers of participants are recruited and that results are generalisable outside Poole, where the intervention was developed.

### Setting

The trial is taking place in three centres (Poole, Bristol, Southampton/Portsmouth) and each centre has a team of trained facilitators to deliver the fatigue management programme.

### Ethical, governance and management considerations

This trial has been reviewed and given a favourable opinion by the North Somerset and South Bristol Multi-Centre Research Ethics Committee (ref: 08/H0106/2). Poole Hospital NHS Foundation Trust is acting as sponsor. The study is funded by a project grant awarded by the Multiple Sclerosis Society of Great Britain and Northern Ireland. The study is included in the National Institute of Health Research Clinical Research Network (NIHR CRN) portfolio (ID 4843).

As the trial involves people with MS and fatigue, careful consideration will be given to the location of the intervention (e.g. public transportation, car parking, walking distances), and the comfort of the participants (room temperature, refreshment breaks, cushioned chairs etc.). Because participants will have fatigue, the length of sessions in the fatigue management programme has been kept reasonably short, and the number and length of outcome measures have been kept to a minimum. Two facilitators will run each session. If someone becomes emotionally upset or unwell during a session, one of the facilitators can take that person aside, and provide information regarding help and support available from local MS services (such as a MS Specialist Nurse), the MS Society and MS Trust, and primary care (General Practice, counselling services etc.).

A trial steering group will meet at regular intervals throughout the trial.

### Service user support

There has been service user involvement in all stages of the research so far, including the development of this protocol. Service users will be represented on the trial steering group.

### Data protection

All information that is collected will be kept strictly confidential and any information that leaves Poole Hospital will not contain any personal details. Questionnaires will be allocated a participant identification number; they will not contain any names or identifying details. Only the authorised members of the research team will have access to the trial data.

### Participants

#### Sample size

Sample size consideration is mostly based upon fatigue as the primary outcome measure; this is the outcome measure used most frequently in other trials that include people with fatigue. As a variety of fatigue measures have been used in other trials, we have used standardised effect sizes to enable comparisons between them. Standardised effect sizes of 0.2 are commonly considered small, 0.5 considered medium, and 0.8 considered large [47]. In this trial, we will aim to detect a medium effect size. The Cochrane systematic review of cognitive behavioural therapy in people with CFS [38] identified two good quality studies, and in these the standardised effect sizes for fatigue were 0.7 and 1.0. The Cochrane Systematic Review of Amantadine for fatigue in MS found effect sizes of between 0.3 and 1.4 for the three studies that measured fatigue on a continuous scale [21]. Thus, our choice of an effect size seems reasonable in the context of (a) how well cognitive behavioural approaches work in another chronic disease where fatigue is a major symptom, and (b) how well another treatment for fatigue works in MS. For 85% power, the sample size requirement (using a two-tailed 5% significance level) is 73 people per arm of the trial; 146 in total. Inevitably, there will be some participants who withdraw from the trial during its course, or more generally, do not complete outcome measures. To allow for this, we will aim to enrol 180 participants; 90 in each arm of the trial. Thus, if 20% of participants do not provide data on the primary outcome measures, the study would maintain statistical power. This figure of 20% will be reviewed during the study and sample size adjusted up or down accordingly.

### Eligibility criteria

#### Inclusion criteria

1. Providing written informed consent.

2. Over the age of 18.

3. Clinical diagnosis of relapsing-remitting or progressive multiple sclerosis (Poser/McDonald criteria [48-50].

4. Score on the Fatigue Severity Scale (FSS) [51] greater than 4. The FSS is a uni-dimensional self-report measure consisting of 9 items that ask about severity of fatigue related to daily activities (such as physical functioning, exercise, work, family, and social life). Responses are made on a 7-point Likert-type scale.

5. Ambulatory (score on the Adapted Patient Determined Disease Steps (APDDS) Scale [52] < 8). This self-administered instrument is based on the Patient-Determined Disease Steps (PDDS) scale and the telephone Expanded Disability Status Scale (EDSS). The programme content will be most relevant for those who are ambulatory. Individuals who are non-ambulatory will continue to receive standard care.

6. Able to attend the intervention sessions.

7. English speaking.

#### Exclusion criteria

1. Attended a specific fatigue management programme within the last year.

2. Received a substantive, specific, fatigue intervention from an Occupational Therapist (OT) or other health professional, consisting of more than general advice, within the previous 3 months (such as the guidance produced by the National Association of Neurological Occupational Therapists (NANOT) [53] (now known as the College of Occupational Therapists Specialist Section - Neurological Practice) [29].

3. Already involved in another research study.

4. Individuals who have cognitive deficits such that they would not be able to engage in the group format or benefit from the programme. If individuals have substantial cognitive deficits much of the content of the fatigue management programme would not be appropriate. This will be based on the judgement of health professionals/local investigators.

5. Individuals who have had a relapse within the previous three months. This would be a potential confound since a change in fatigue could be the result of treatment or improvement after a recent relapse.

6. Individuals who have been on a disease-modifying drug (such as Beta-Interferon, Glatiramer Acetate) or an anti-depressant for fewer than 3 months. One of the possible initial side effects of these drugs is fatigue and thus this could be a confounder.

7. Individuals who are known to be currently under the care of a psychiatrist or under the care of addiction services will be excluded. Ongoing psychiatric disorders or addiction problems would compromise the potential to benefit from the programme.

Individuals excluded from the research project will continue to be seen as per usual care.

#### Source of participants

The recruitment target for each of the three centres will be 60 people, of whom 30 will receive the group-based intervention. In each centre this will require running three successive iterations of the programme, recruiting in blocks of around 20. The fatigue management programme has been designed for groups of between 6-12 participants.

Participants will be recruited using a variety of methods; via MS Services/Neurology Departments, MS Society newsletters and website, other relevant newsletters, MS Research database, MS support groups, General Practitioners.

#### Recruitment and consent

Potential participants (identified via secondary or primary care or self-referred) will be sent a trial information pack (Key Facts sheet, a set of Participant Information Sheets, two screening measures (FSS & APDDS), response slips (interested to hear more/decline to participate, plus reasons why) and a prepaid envelope. They will be asked to return a reply slip and the two completed screening measures in a prepaid envelope to the Local Investigator (LI) if they wish to find out more about the trial, or a decline slip, if they would prefer not to receive any further information. Individuals who have not responded will be sent a second trial information pack two weeks later and a final invitation to participate one month later.

The LI in each centre will telephone those who have expressed an interest in the trial and give them an opportunity to ask questions. If, after this discussion, the individual still wishes to take part, the LI will undertake a screening using a checklist. After screening, participants will be notified via the telephone whether they are eligible or ineligible. Participants who are currently ineligible (e.g. due to medication recently started, a planned holiday, having received fatigue advice etc.) but who may fulfil eligibility criteria at a later date will be held over to be rescreened (if another iteration is scheduled in the centre). Individuals who are ineligible will be sent a letter notifying them of this, along with a booklet produced by the MS Society about MS-fatigue [54].

#### Randomisation

To ensure good allocation concealment, random allocation will be e-mail-based and administered at Poole Hospital by the statistician who will be blinded to the identity of participants. Once a block of participants from a centre have provided informed consent they will be formally entered onto the trial database and an anonymised list of their identification numbers will be sent to the statistician who will randomly allocate half to the FMP group and half to the current local practice group. This method implies stratification by centre.

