## Results

### Statistical analysis

We will conduct two sets of statistical analyses. The primary analysis will be an intention-to-treat analysis, whereby participants are analysed in the arm of the trial they were randomised to, regardless of how many sessions of the programme they attend. In order for an intention-to-treat analysis to be conducted, we will endeavour to collect outcome measures for everyone (while recognising the right of participants to withdraw from the trial at any stage). The secondary analysis will be conducted on a "per protocol" basis. This analysis will exclude participants who attend fewer than four sessions of the fatigue management programme.

Data will be analysed primarily using SPSS for Windows. A 5% significance level will be used. Outcome measures will be assumed to be interval scaled, and the analysis will initially be focused on absolute change in outcome post-intervention relative to baseline, and absolute change in outcome at 4- and 12-month follow-up, relative to baseline. These change scores, presented separately for the three follow-up periods, are being used because we think they are the most clinically useful. They are likely to be normally distributed (this assumption will be checked). Change scores will be compared between the two groups using the independent samples *t*-test.

Additional analyses will be conducted to address the following issues:

1. We will adjust for baseline variability/baseline differences between treatment arms. For each outcome variable analysed, these would include the baseline measurement for that outcome, baseline primary outcome measures, gender, age, marital status, education level, type of MS, time since diagnosis, and level of disability.

2. Although participants in the trial have been randomised individually, for those randomised to the fatigue management intervention, it is possible that the group-based nature of the intervention will result in observations that are clustered. This could result in misleading statistical tests [74]. We will assess the extent to which this occurs by incorporating clustering into the analysis.

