3. It is likely that outcome data will be missing for some participants. In the main analysis such individuals will be excluded. However, the implied assumption that the data are "Missing Completely At Random" might not be correct, potentially leading to biased estimates of the effect of the intervention [75]. Two methods will be used to assess the extent to which this occurs: Firstly, we will use the "Last Observation Carried Forward" imputation method (which assumes no change in outcome when a data point is missing). Secondly, we will use a mixed model for repeated measurements.

4. Analysing the change in outcome from baseline to each time point will, we believe, result in the most clinically useful presentation of results. However, to gain a deeper understanding of how outcome measures change over the course of follow-up, we will also model all measurement occasions together for each outcome.

5. It is possible that the fatigue management programme might be more effective in certain sub-groups of individuals. We will examine these potential effect modifiers by testing the relevant "treatment x effect modifier" interaction terms. However, we acknowledge that these statistical tests are likely to be underpowered, since this was not a specific aim of the study. In these analyses, we will consider study centre, baseline fatigue, gender, age, marital status, type of MS, time since diagnosis, and level of disability.

These additional analyses will involve the use of a variety of techniques including multi-level/mixed models. In addition to these pre-specified analyses, we will also conduct further exploratory analyses as suggested by the data.

Presentation of the results will follow the Consolidated Standards of Reporting Trials (CONSORT) [76,77] guidelines, in such a way that they can be meaningfully incorporated into systematic reviews. The design of the trial will help ensure that it is graded as high quality in systematic reviews.

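### Allocation is balanced within centre-by-iteration blocks, but the main t-test and the adjusted model's covariate list include neither centre nor block, which makes the test mildly conservative

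*Protocol article*

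**What the plan says.** Under Source of participants, the protocol article plans 60 people in each of three centres, recruited in blocks of around 20 over three successive iterations. Under Randomisation, a block is allocated once its members have consented, half to the fatigue management programme (FMP) and half to current local practice. The article draws the consequence itself: "This method implies stratification by centre".

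Under Statistical analysis, the main comparison is an independent samples t-test on change from baseline at each follow-up. It has no stratum term. Additional analysis 1 adjusts for baseline variables and spells them out: "these would include the baseline measurement for that outcome, baseline primary outcome measures, gender, age, marital status, education level, type of MS", followed by time since diagnosis and disability. Centre, iteration and block are absent. Additional analysis 5 does name centre, but only as a possible effect modifier: "In these analyses, we will consider study centre, baseline fatigue, gender, age", and so on. The article expects those interaction tests to be underpowered. Additional analysis 2 will bring clustering into the analysis because the FMP is delivered in groups; it does not say which levels the model will have.

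**The concern.** When allocation is balanced within strata, differences between strata cancel out of the treatment contrast. An analysis that does not know the strata still counts those differences as residual error. Its standard error is then larger than the true sampling variability of the estimate, so intervals are too wide, p-values too large and some power is given away.

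The documents offer reasons why blocks could differ in change scores. Both arms of a block are sent questionnaires on the same dates (Outcome Measures), so they share calendar time. The Background describes fatigue that heat triggers or worsens. The Control group section says usual care varies within and between centres.

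This is not a detail left for an analysis plan. The article fixes the test and writes out the covariates, including marital status and education, while leaving out the one factor that it says the randomisation is stratified by.

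**Working it through.** **Step 1. Reproduce the plan's own figure.** Inputs from Sample size: "For 85% power, the sample size requirement" is computed "using a two-tailed 5% significance level"; the target is medium ("In this trial, we will aim to detect a medium effect size"), with "0.5 considered medium"; the result "is 73 people per arm of the trial; 146 in total". The exact noncentral-t calculation for a difference of 0.5 SD gives 73 per arm (power 0.851); the normal approximation gives 72. The figure reproduces. Enrolling 180 and losing 20% leaves 180 × 0.8 = 144, or 72 per arm, with power 0.846.

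**Step 2. Count the strata.** 3 centres × 3 iterations = 9 blocks of about 20. With 20% loss, 20 × 0.8 = 16 per block, or 8 + 8.

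**Step 3. Size of the standard error.** Let s be the share of change-score variance that lies between blocks. The documents give no value, so s from 0 to 0.20 is assumed. With total variance set to 1 and n per arm:

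- true variance of the treatment difference, block effects having cancelled: 2(1 − s)/n
- variance that the plain t-test estimates: about 2/n
- ratio of reported to true standard error: 1/√(1 − s)

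This gives 1/√0.95 = 1.026, 1/√0.90 = 1.054 and 1/√0.80 = 1.118, so the standard error is about 2.6%, 5.4% or 11.8% too large.

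**Step 4. Effect on the test.** Simulation of 9 blocks with 8 + 8 evaluable participants, random block effects, no therapy-group effect and 40,000 runs per scenario, comparing the plain t-test with a linear model that includes block (144 − 10 = 134 residual degrees of freedom):

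| s | Type I error, plain | Type I error, with block | Power at 0.5 SD, plain | Power at 0.5 SD, with block |
|---|---|---|---|---|
| 0 | 0.050 | 0.051 | 0.846 | 0.846 |
| 0.05 | 0.045 | 0.050 | 0.856 | 0.867 |
| 0.10 | 0.041 | 0.050 | 0.859 | 0.879 |
| 0.20 | 0.032 | 0.052 | 0.879 | 0.915 |

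Power differences are 0, 0.011, 0.020 and 0.036, that is about 0, 1, 2 and 4 points. A repeat with a different random seed gave the same pattern, with the mean estimated difference at its true value (0 or 0.5) to within about 0.002, so there is no bias.

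**Step 5. Cost of the term when it is not needed.** At s = 0 the two analyses have the same power, 0.846. Block uses 9 − 1 = 8 degrees of freedom and centre 3 − 1 = 2.

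**The case against.** The strongest reply is that the harm is small and in the safe direction. That stands. The estimate is unbiased, type I error does not exceed 5% from this cause, and the plain t-test keeps power at about 0.85 to 0.88 over the assumed range. The share s may also be small: change scores remove stable differences in level between centres, the article calls variation in usual care minor, and nothing in it says that season moves these particular scales. At s of 5% or less, the loss is about one point of power.

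Three stronger readings are tempting and not supported.

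- A reader might equate the loss with discarding 5% to 15% of the sample. That holds for interval width but not for power, because balanced allocation has already taken block variance out of the estimate. At s = 0.10 the plain test loses about 2 points against the block-adjusted analysis. Losing 10% of participants from that adjusted analysis would cost about 3.6 points (0.881 to 0.845, noncentral t).
- A reader might infer that the whole analysis ignores the strata. It does not: centre is considered in the interaction tests, although these do not put it into the main treatment-effect estimate.
- A reader might conclude that block effects will be confused with FMP group effects in the clustering analysis. That presumes a model without a block or centre term. The article mentions multi-level and mixed models but does not specify their levels, so this is a risk to guard against and not an error in the text.

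It is also fair that the article names stratification by centre only. Stratification by iteration follows from allocating block by block, but the article does not state it.

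**Conclusion.** The point holds in a limited form. The omission is certain: the article declares stratification by centre, balances allocation within about nine blocks, and then fixes a main test and a covariate list without centre or block. The consequence is modest and conditional. If blocks explain 5% to 20% of change-score variance, the test runs at about 0.045 to 0.032 in place of 0.05 and gives up about 1 to 4 points of power relative to a block-adjusted analysis; if they explain nothing, nothing is lost. The planned 85% power is not breached by this cause. The slight shortfall to 0.846 at 72 per arm comes from 144 evaluable participants against the 146 required.

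These figures assume equal evaluable numbers in each half-block, block effects common to both arms and no clustering by therapy group. Such clustering is a separate matter and works in the opposite, anti-conservative direction. The change is worth making because it is nearly free, not because the planned result would mislead.

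**What to change.** Replace the plain t-test with a linear model for the change score that contains treatment and randomisation block (centre × iteration) as fixed effects, or at least centre. The change score stays as the outcome, so the presentation that the article prefers is kept. Add the same term to the covariate list in additional analysis 1. Carry it in the clustering model of additional analysis 2, so that centre or season effects shared by both arms of a block are not read as therapy-group clustering. In the Randomisation section, state that allocation is balanced within centre and iteration.

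The cost is about 8 degrees of freedom for block or 2 for centre. Both are known for every participant, so no new data are needed, and the sample size need not change.
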